**Method**

**Inclusion criteria**

Maternal age ≥ 18 years old, singleton pregnancy and fetal survival at 11^+0^ to 13^+6^ weeks of gestational age, history of chronic hypertension defined as hypertension diagnosed before pregnancy or at the first prenatal visit.

**Exclusion criteria**

Severe cardiovascular or respiratory disease, hyperthyroidism, pregestational diabetes mellitus, incompetent cervix, recurrent spontaneous abortion, a history of spontaneous preterm birth, threatened abortion or inevitable abortion, placenta praevia, severe anemia, malnutrition or very low body weight (body mass index < 12kg/m2), with severe mental disorders and disable to express their will, with other obvious abnormal signs, laboratory examination and other clinical diseases.

**Diagnostic criteria** (2020 Chinese Guidelines for the Diagnosis and Treatment of Hypertensive Diseases during Pregnancy)

**Preeclampsia**

Systolic blood pressure ≥140mmHg and/or diastolic blood pressure ≥90mmHg after 20 weeks of gestation, accompanied by any of the following: urinary protein quantity ≥0.3g/24h, or urinary protein/creatinine ratio ≥0.3, or urinary protein ≥ (+); or accompanied by following damages of organs involved: heart, lung, liver, kidney and other important organs, or abnormal in the digestive system, nervous system, placenta - fetal involvement, etc.

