**Method**

**Inclusion criteria**

1. Aged ≥18 years;

2. 11-13+6 weeks of gestation;

3. Pregnant women at high risk for preeclampsia;

4. Single pregnancy and fetal survival;

5. Understand and sign the consent form.

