Chronic hypertension is estimated to affect 0.3% to 4.3% of pregnant women, and the risk of preeclampsia is 5.43 times in women with chronic hypertension than in those with normotensive. Furthermore, chronic hypertension was associated with a higher risk of cesarean section, maternal mortality, preterm birth, stillbirth, small for gestational age (SGA), low birth weight, and neonatal intensive unit admission [3, 4]. The abovementioned maternal and adverse perinatal outcomes are prone to occur in chronic hypertension-superimposed preeclampsia compared with preeclampsia alone [5, 6]. Blood pressure management is substantial throughout the perinatal period of pregnant women with chronic hypertension. Two large randomized trials [7, 8] found that antihypertensive treatment targeting a blood pressure <140/90 mmHg in chronic hypertension was safe and beneficial for maternal and neonatal. However, some agents should be avoided in pregnancy owing to the possible or proven concerns about fetotoxicity [9-11]. Pregnant women have limited options for antihypertensive medications compared with non-gestational. Pregnant termination should be considered to avoid maternal and fetal complications such as placental abruption and cardiovascular and cerebrovascular adverse events when hypertension is uncontrollable after active treatment. Lifestyle modifications can enhance the effects of antihypertensive therapy. Guidelines for gestational hypertension of pregnancy and non-gestational [12-14] had recommended lifestyle modifications, including salt reduction, smoking and alcohol cessation, healthy diet and drinking, weight reduction, and regular physical activity.

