1.2 Laboratory Examination

Folic acid, vitamin B12, fasting blood glucose, blood routine, urine routine, kidney function, blood lipid, coagulation function, liver function, thyroid function.

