2.2 The presentation of preeclampsia

Systolic blood pressure ≥140mmHg and/or diastolic blood pressure ≥90mmHg after 20 weeks of gestation, accompanied by any of the following: urinary protein quantity ≥0.3g/24h, or urinary protein/creatinine ratio ≥0.3, or urinary protein ≥ (+); or accompanied by following damages of organs involved: heart, lung, liver, kidney and other important organs, or abnormal in the digestive system, nervous system, placenta - fetal involvement, etc.

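### The pre-eclampsia outcome does not require new-onset proteinuria or organ involvement, so in this chronic-hypertension cohort pre-existing disease plus one qualifying blood pressure after 20 weeks counts as an incident case

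*Supplement*

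**What the plan says.** The supplement holds two protocols. The later one, reviewed here, concerns women with chronic hypertension.

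- **Population** (Inclusion criteria): "history of chronic hypertension defined as hypertension diagnosed before pregnancy or at the first prenatal visit", enrolled at 11+0 to 13+6 weeks.
- **Outcome definition** (Diagnostic criteria, Preeclampsia): "Systolic blood pressure ≥140mmHg and/or diastolic blood pressure ≥90mmHg after 20 weeks of gestation, accompanied by any of the following: urinary protein quantity ≥0.3g/24h". A urinary protein/creatinine ratio, a dipstick result, or damage to the heart, lung, liver, kidney and other systems also qualifies.
- **Follow-up section** (2.2 The presentation of preeclampsia): the same rule again, "accompanied by any of the following: urinary protein quantity ≥0.3g/24h, or urinary protein/creatinine ratio ≥0.3, or urinary protein ≥" (+), with no comparison against baseline.
- **Exclusion criteria**: severe cardiovascular or respiratory disease is named, and there is a general clause for other abnormal signs, laboratory results and diseases. Kidney disease and proteinuria are not named. Kidney disease is a medical-history item at registration (1.1).
- **Baseline tests** (1.2 Laboratory Examination): the list includes "urine routine, kidney function", blood routine and liver function. It includes no 24-hour urine protein and no protein/creatinine ratio.
- **Background**: adverse outcomes are described as "prone to occur in chronic hypertension-superimposed preeclampsia compared with preeclampsia alone", so the plan recognises superimposed disease as a separate condition. No outcome defines it.
- **Use of the outcome** (Outcomes; Data analysis): incidence is exploratory, and so is the effect of exercise on BP control among women with pre-eclampsia. Relative risks with 95% confidence intervals are planned.

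**The concern.** The definition is identical to the one in the supplement's earlier protocol for women at high risk of pre-eclampsia. Carrying text over is no fault in itself. What matters is whether the text fits a cohort in which everyone already has hypertension.

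A case needs two things: a raised BP after 20 weeks, and proteinuria or organ involvement. For a woman whose proteinuria or organ damage predates the study, the second component is met on entry. Whether she becomes a case then depends only on whether her BP reaches the threshold. An event reported as new pre-eclampsia may be long-standing renal or organ disease plus one raised reading.

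Three results are exposed:

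- the incidence itself, which is inflated;
- the relative risk, which is diluted if such women are equally common in both groups and biased if they are not;
- the subgroup for the second exploratory outcome, which would mix new with pre-existing disease.

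There is also a problem of interpretation. For these women the outcome repeats what the BP endpoints already measure, so a BP difference alone could be read as prevention of pre-eclampsia.

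**Working it through.** **1. The plan's own figure.** The plan gives no figure for pre-eclampsia; its only calculation is for 24-hour ambulatory SBP. Inputs (Data analysis): changes of −7.3 (SD 12.7) and 1.1 (SD 8.2), so the difference is 8.4 mmHg; two-sided 0.05; 36 per group; 90% power; 20% attrition.

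- SD = √[(12.7² + 8.2²)/2] = 10.69.
- The normal approximation gives 35 per group. Noncentral-t power at 36 per group is 90.8%.
- 72/(1 − 0.20) = 90.

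The stated size reproduces, and the pre-eclampsia definition plays no part in it.

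**2. How the definition classifies women.**

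| Woman at baseline | BP below 140/90 throughout, after 20 weeks | BP at or above 140 and/or 90 after 20 weeks |
|---|---|---|
| No proteinuria or organ damage | not a case | case only if a qualifying finding appears |
| Proteinuria or organ damage already present | not a case | case, with nothing new required |

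The lower right cell is the problem.

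**3. Size, on assumptions.** The documents give neither the prevalence of baseline proteinuria nor the pre-eclampsia risk.

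- Assumed new-onset risk in the light-activity group: p₀ = 0.30.
- Assumed effect: OR 0.59, the meta-analysis figure in the Background. Odds = (0.30/0.70) × 0.59 = 0.2529, so p₁ = 0.2529/1.2529 = 0.202. True RR = 0.202/0.30 = 0.67.
- f = share of a group with both pre-existing proteinuria and a qualifying BP after 20 weeks, assumed equal in the two groups.
- Observed risk = f + (1 − f)p.

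| f | Light group | Moderate group | Observed RR | Non-incident cases per 36 (36 × f) | Share of light-group cases |
|---|---|---|---|---|---|
| 0 | 0.300 | 0.202 | 0.67 | 0 | 0% |
| 0.05 | 0.335 | 0.242 | 0.72 | 1.8 | 0.05/0.335 = 15% |
| 0.10 | 0.370 | 0.282 | 0.76 | 3.6 | 0.10/0.370 = 27% |
| 0.15 | 0.405 | 0.322 | 0.79 | 5.4 | 0.15/0.405 = 37% |

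Varying the light-group risk from 15% to 35% and f from 5% to 20% moves a true RR of 0.63 to 0.69 to an observed 0.72 to 0.86.

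**4. Unequal shares.** Groups are formed by observed activity (Grouping scheme), so f need not be equal. Take no true effect and p = 0.30 in both groups. With f = 0.15 in the light group and 0.05 in the moderate group, RR = 0.335/0.405 = 0.83. With the shares swapped, RR = 0.405/0.335 = 1.21. The documents do not indicate which direction applies.

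**The case against.** **BP is still required.** A reader might infer that any woman with baseline proteinuria becomes a case at 20 weeks whatever her activity. The documents do not support that. She must also reach 140 and/or 90 after 20 weeks, which is not inevitable: the Background describes antihypertensive treatment targeting values below 140/90. BP is also the quantity that activity is expected to change. This objection stands in full, and it is why f above is the share meeting both conditions, not the prevalence of proteinuria.

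**Reverse causation.** A reader might infer that renal involvement makes women less active, giving a spurious benefit. Nothing in the documents says so. What stands is only that the groups are not randomised, so imbalance in either direction is possible.

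**The effect size.** Reading the 0.59 as a relative risk would overstate the starting effect. It is an odds ratio, equivalent to an RR of 0.67 at 30% risk.

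**Partial safeguards.** The general exclusion clause might remove some women with marked renal abnormality, and severe cardiovascular or respiratory disease is excluded by name. The general clause, however, sets no threshold and does not mention proteinuria. The diagnostic heading cites a national guideline that may treat superimposed disease separately. That source cannot be checked here, and the written criterion imports no such rule.

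**Exploratory status.** This also stands. At 36 per group, power for OR 0.59 is only 11% to 17% with a clean definition (light-group risk 15% to 35%), so no confirmatory conclusion rests on this outcome. That limits the severity, but a planned relative risk should still count what its name says.

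**Conclusion.** The point holds in limited form. As written, the rule can count pre-existing proteinuria or organ damage as incident pre-eclampsia once BP reaches the threshold after 20 weeks. That is a misclassification built into the definition, not just missing detail.

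Its reach is the exploratory incidence outcome, its relative risk, and the subgroup used for the second exploratory outcome. A reader should not infer that the primary ambulatory SBP comparison or the sample size of 72 (90 recruited) is compromised; neither uses this definition.

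The illustrated dilution, from an RR of 0.67 to between 0.72 and 0.79, rests on an assumed 30% risk, the quoted OR of 0.59, and assumed equal shares of 5% to 15%. None of the shares or risks comes from the documents. If few women enter with proteinuria, or few of them reach the BP threshold, the effect is small. The change is worth making because it is cheap, not because the harm is known to be large.

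**What to change.** For endpoint counting, define the outcome as superimposed pre-eclampsia: the qualifying proteinuria or organ finding after 20 weeks must have been absent at the 11 to 13+6 week baseline. Judge absence from the urine routine, kidney, liver and blood results already collected then.

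Report women with baseline urine protein of (+) or more, or known kidney disease, separately by group. Either leave them out of the incidence relative risk or show it with and without them. Because they are identified by baseline data, this does not select on the outcome. Use the same definition to form the pre-eclampsia subgroup.

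Put identical wording under Diagnostic criteria (Preeclampsia) and under 2.2 The presentation of preeclampsia.

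The cost is endpoint wording in two places and no new tests. There will be somewhat fewer events and, in the analysis without these women, a smaller denominator: if 10% had baseline proteinuria, 72 × 0.10, or about 7 women. Baseline proteinuria can be judged only on the urine routine, since no 24-hour protein or protein/creatinine ratio is listed at baseline. This is a rule for counting events and changes nothing in the women's care.

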**Grouping scheme**

1. Grouping method: During early pregnancy (11~13+6 weeks), an ActiGraph wGT3X-BT exercise accelerometer will be worn on the wrist to monitor the intensity, time, number of steps and energy metabolism of daily physical activity within 1 week, and the number of exercise steps will be collected by mobile phone APP. Participants will be divided into light and moderate groups according to the activity intensity of early pregnancy. Moderate-intensity activity is defined as 150 minutes per week, and the light-intensity activity group has a activity intensity or activity time of fewer than 150 minutes per week.

2. Drug intervention plan: pregnant women in both groups take low-dose aspirin 100mg daily from 11 to 13+6 gestational weeks until 2 to 7 days before termination or 34 gestational weeks as recommended by the guidelines. Oral calcium supplementation should be at least 1 g/ day.

3. Health guidance: limit salt intake (<6 g/d), smoking cessation, regular rest, weight control, etc.

4. Exercise monitoring: Wear an ActiGraph wGT3X-BT exercise accelerometer on wrist to monitor physical activity for a week. Except for bathing, swimming and other contacts with water, the rest of the time should be worn as required, ensure that more than 10 hours of wear every day, and at least two working days (Monday to Friday), rest day (Saturday to Sunday) with one day of valid data.

1) Activity intensity: light physical activity (100 -1952 CPM) and moderate physical activity (≥1952 CPM). Data were collected by ActiLife 6.0 analysis software after completion.

2) Active metabolic rate: measured by average metabolic equivalents (METs).

3) Perceived exertion rating: ratings of perceived exertion (RPE) based on the Borg perceived Exertion Scale (Table 1) are used. The Borg scale has 15 ratings ranging from 6 to 20, representing different levels of fatigue, with 6 being "very, very easy" and 20 beings "very, very difficult". For moderate-intensity exercise, the RPE score of pregnant women should be 13 to 14 points, that is, the feeling of self-exercise intensity is somewhat difficult.

[figure not shown]

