**Outcomes**

1. Primary outcome: the difference in 24-hour ambulatory systolic blood pressure change from baseline during the third trimesters of pregnancy;

2. Secondary outcomes: the difference in 24-hour ambulatory systolic blood pressure change from baseline during the second trimesters of pregnancy; the difference of daytime and nighttime ambulatory blood pressure, daytime and nighttime and 24-hour diastolic blood pressure, and clinic blood pressure changes from baseline;

3. Exploratory outcomes: incidence of preeclampsia; effect of exercise on blood pressure control in pregnant women with preeclampsia

4. Safety outcomes: activity tolerance decline rate; incidence of shortness of breath; incidence of heart failure;

5. Other relevant outcomes: severe complications of preeclampsia (eclampsia, heart failure, pulmonary edema, HELLP syndrome, DIC), fetal death, iatrogenic premature delivery, neonatal asphyxia, NICU. Compliance with oral aspirin and calcium; mobile phone exercise recording monitoring exercise intensity compliance; the Subjective Exertion Scale (RPE) monitors an individual's exercise intensity tolerance.

[figure not shown]

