**Data analysis**

The study is powered for the primary outcome measure of change in 24-hour ambulatory SBP from the first to the third trimester. The sample size calculation was based on the results of Lopes S et al.[14], who showed a decrease of -7.3 ± 12.7mmHg in 24-hour ambulatory SBP in the exercise group with 1.1 ± 8.2mmHg in the control group. A sample of 72 pregnant women (36 per group), with a two-sided significance level of 0.05, provided 90% statistical power to demonstrate this difference in 24-hour ambulatory SBP. In order to accommodate a 20% attrition rate, 90 pregnant women will be recruited (PASS11, independent t-tests; allocation ratio = 1).

Continuous variables will be presented as means ± standard deviations or median (interquartile range) according to normal distribution or not. Between-group differences at baseline will be tested with Student’s independent t-test or Mann–Whitney U test. For the categorical variables, results will be expressed as counts and percentages. Categorical variables will be tested with the chi-square test or Fischer test if appropriate between groups at baseline. The assessment of compliance with daily physical activity and safety will be summarized for the two groups. A cut-off of 80% of baseline physical activity during the second and third trimesters will be used to determine compliance well. Adverse events, if any, will be reported. The primary outcome and difference of the change in 24-hour ambulatory SBP from the first to the second trimester between groups will be analyzed using analysis of covariance, adjusting for baseline blood pressure. Other secondary outcomes will be analysis using general linear modelling to compare the difference of blood pressure change in the MPA and LPA groups at the second and third trimesters, adjusting for baseline blood pressure. The analyses will be conducted based on the intention-to-treat principle. The intention-to-treat population will comprise all the patients with the exception of those who do not complete ambulatory blood pressure measurement and physical activity monitoring at 3-time points for any reason, such as miscarriage, or preterm birth. Per-protocol set will be performed as a sensitivity analysis. Relative risks and 95% confidence intervals will also be provided. A two-sided p-value below 0.05 will be considered statistically significant in all analyses. Data will be analyzed using SPSS 25 statistical software.

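### In a cohort of women with chronic hypertension, the pre-eclampsia case definition requires BP of at least 140/90 and does not require new features, so incidence and any relative risk depend partly on BP level

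*Supplement*

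**What the plan says.** All references are to the chronic-hypertension protocol in the Supplement.

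- **Population.** Inclusion criteria: "history of chronic hypertension defined as hypertension diagnosed before pregnancy or at the first prenatal visit".
- **Case definition.** Diagnostic criteria, Preeclampsia, repeated under Follow-up data registration, item 2.2: "Systolic blood pressure ≥140mmHg and/or diastolic blood pressure ≥90mmHg after 20 weeks of gestation, accompanied by any of the following", followed by three proteinuria criteria, "or accompanied by following damages of organs involved: heart, lung, liver, kidney and other important organs" and other systems. Both branches are attached to the BP condition. Neither is required to be new or worse than at entry. The text does not say whether the reading is clinic or ambulatory, or single or repeated. The same wording appears in the Supplement's other protocol, which enrols women at high risk of pre-eclampsia.
- **Superimposed disease.** The Background says that adverse outcomes are "prone to occur in chronic hypertension-superimposed preeclampsia compared with preeclampsia alone", but superimposed pre-eclampsia is never defined.
- **Use in analysis.** Outcomes, item 3: "Exploratory outcomes: incidence of preeclampsia; effect of exercise on blood pressure control in pregnant women with preeclampsia". Data analysis: "Relative risks and 95% confidence intervals will also be provided", without naming the outcome.
- **Treatment.** The Background reports from two other trials that "antihypertensive treatment targeting a blood pressure <140/90 mmHg in chronic hypertension was safe and beneficial for maternal and neonatal". The study's own plan begins "Drug intervention plan: pregnant women in both groups take low-dose aspirin 100mg daily", adds calcium, and sets no antihypertensive rule or target.

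**The concern.** In women who enter normotensive, crossing 140/90 after 20 weeks helps to mark onset. In women who enter with hypertension, it largely reflects how high their BP runs. Used unchanged here, the condition ties the case count to BP level.

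The study's hypothesis is that moderate activity lowers SBP. If it does, fewer women in the moderate group meet the BP condition, and fewer are labelled pre-eclamptic, even if proteinuria and organ damage are equally common in both groups. The Background hopes for both prevention of pre-eclampsia and better BP control, and this definition cannot separate the two. The second half of the exploratory item is also affected: BP control would be compared within a subset selected on BP.

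**Working it through.** **1. The plan's own figure.** Difference: 1.1 − (−7.3) = 8.4 mmHg. Pooled SD: √((12.7² + 8.2²)/2) = √114.27 = 10.69. By the noncentral t at two-sided 0.05, power is 89.98% with 35 per group and 90.8% with 36. Then 72/(1 − 0.20) = 90. The stated sample size reproduces and does not depend on the case definition.

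**2. Who is counted, read literally.**

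| BP after 20 weeks | Proteinuria or organ feature | Case? |
|---|---|---|
| Below both limits at every reading | New | No |
| At or above a limit at any reading | New | Yes |
| At or above a limit | Present before 20 weeks, unchanged | Yes |

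The third row is possible in this cohort. History of kidney disease is recorded at registration (item 1.1) and is not named among the exclusions.

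**3. Effect on the RR.** In each group let a be the share with a new feature, b the share with only an old feature, and g the probability of meeting the BP condition. Suppose first that g is unrelated to the feature. Observed incidence is (a + b)g, so

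RR = [(a_M + b_M) g_M] / [(a_L + b_L) g_L].

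- With a and b equal in both groups, RR = g_M/g_L: the BP result restated.
- With a true difference in a, equal b dilutes it towards 1, and unequal b can move the RR either way.
- The groups are formed from observed activity, so g may differ for other reasons. With no activity effect, g = 0.4 against 0.6 (assumed) gives 0.67, and the reverse gives 1.5.

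**4. Size under assumptions.** The documents give no follow-up SBP distribution, no share below 140/90 and no pre-eclampsia rate. Only the 8.4 mmHg is theirs; every other input here is assumed.

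*(i) One systolic reading, unrelated to disease.* g_L = 1 − Φ((140 − μ)/σ) and g_M = 1 − Φ((140 − μ + δ)/σ), with light-group mean μ 134–152 and SD σ 12–18.

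| μ, σ | g_L | g_M, δ = 8.4 | RR, δ = 8.4 | RR, δ = 3 |
|---|---|---|---|---|
| 134, 12 | 0.309 | 0.115 | 0.37 | 0.73 |
| 140, 15 | 0.500 | 0.288 | 0.58 | 0.84 |
| 152, 18 | 0.748 | 0.579 | 0.77 | 0.93 |

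Lower means give lower ratios: at μ = 125, σ = 10, 0.0096/0.0668 = 0.14.

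*(ii) Disease itself raises SBP.* With μ = 130, σ = 12:

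| Rise in true cases | RR, δ = 2 | RR, δ = 8.4 |
|---|---|---|
| 20 mmHg | 0.748/0.798 = 0.94 | 0.553/0.798 = 0.69 |
| 30 mmHg | 0.933/0.952 = 0.98 | 0.833/0.952 = 0.87 |

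*(iii) Any one of several readings suffices.* Take μ 134–152, a 15 mmHg rise in true cases, between-woman SD 12, within-woman SD 9, k = 4 or 8 readings, and g = E[1 − Φ((140 − m − 12Z)/9)^k], where m is the group mean and Z is standard normal. The RR is 0.96–1.00 at 3 mmHg and 0.84–0.99 at 8.4 mmHg.

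**5. Precision.** With 36 per group and incidence p in both groups, SE(log RR) = √(2(1 − p)/(36p)). At p = 0.15 the 95% interval around RR = 1 is 0.33–3.00; at p = 0.35 it is 0.53–1.88.

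**The case against.** A reader might infer that this is a treated cohort in which women controlled below 140/90 can never be cases, so that the RR is biased downwards by a known amount. The documents do not support that:

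- **Treatment.** Antihypertensives are not an entry requirement, and the 140/90 target describes other trials.
- **"Never".** The condition is systolic and/or diastolic, with no repeat or sustained elevation required. One raised reading with a feature qualifies, so only women below both limits at every reading are missed.
- **Size.** The larger biases need BP to be unrelated to disease and a single systolic reading. When disease raises BP, or several readings count, much of the bias goes. The 8.4 mmHg is a 24-hour ambulatory difference from an exercise trial in refractory hypertension, applied here to a threshold with no stated measurement method.
- **Direction.** Old proteinuria can be counted, so error also runs the other way.
- **Stakes.** The outcome is exploratory, the groups are not randomised, and the interval for the RR is wide.

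All of this stands and limits the claim. It does not remove the structural fault. Both branches require BP at or above a limit, no feature need be new, and superimposed pre-eclampsia is undefined in a protocol made up entirely of women with chronic hypertension. A wide interval does not excuse an estimate that partly restates the primary result.

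There is also a fair objection to dropping the BP condition altogether. Isolated fetal growth restriction or raised liver enzymes from another cause could then count as cases. That argues for reporting both versions, not for replacing one with the other.

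**Conclusion.** The point holds in limited form. The case definition is not fitted to the population, and the resulting misclassification depends on BP level and runs both ways. A real SBP difference between groups could lower the pre-eclampsia RR with no difference in proteinuria or organ damage.

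Neither size nor net direction can be derived from the documents. Under the assumptions shown, the spurious RR runs from negligible (about 0.98, or nearer 1 if any of several readings counts) to large (about 0.4 at 8.4 mmHg with one reading unrelated to disease; lower still if mean SBP is well under 140). These are illustrations, not estimates of what this study will show. Part of any lower count could be true prevention. The consequence is confined to an exploratory outcome and its interpretation.

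**What to change.** Reconcile the definition (Diagnostic criteria, Preeclampsia; Follow-up item 2.2) and Outcomes item 3 with the chronic-hypertension population, for analysis purposes only:

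1. Require the proteinuria or organ feature to be new or worse after 20 weeks against the woman's own results at 11 to 13+6 weeks, for tests listed at both times: routine urine, kidney function, liver function and blood count (items 1.2 and 2.3). State how features with no listed baseline are handled; 24-hour protein and protein/creatinine ratio are not among the listed tests.
2. Report incidence and RR side by side, with and without the 140/90 condition, and state which BP readings count.
3. Do not read a lower RR as prevention separate from the BP effect unless both versions agree.

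The cost is outcome wording and a little more analysis. No new visit or test is needed for the four listed tests. The version without the BP condition may count some features from other causes, which the side-by-side report will show.
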